To ensure fidelity of the intervention and to prevent clustering, the intervention was designed by the research team. Nevertheless, in this regard the research team consulted with primary health care providers in each practice, specialists, and decision-makers to ensure that the intervention is adapted to the needs expressed. Moreover, interventions will be done by CDPM professionals, recruited and trained by the research team about the general principles of self-management support, patient-centered care, motivational interviewing, interprofessional collaboration and integration of services. The rationale of such a process is to ensure standardization of practices within and across the eight clinics in order to prevent study interventions from evolving differently, as results will be unusable if participants experience different interventions. However, despite the use of such patterns, heterogeneity that may be observed and documented between clinics in terms of outcomes produced, termed “center effects” is part of the pragmatic design and will reflect the clinical reality of primary health care. It has been suggested that interventions may be affected by center-specific issues and characteristics such as degree of sub-specialization within practices and provider background and experience, [52] however, we believe that delivering interventions by practitioners who evolve through the same training process will reduce clustering effects so that the experiment can be replicated across centers and over time [53]. This desired objectivity is based on the involvement of systematic recourse to the collective production of evidence and requires standardization of practices within settings in order to produce replicable findings which can then be used to standardize practice within, and across, clinical care settings [54]. Moreover, efforts will be made to increase the number of participants in each setting in order to reach a certain degree of comparable statistical weight for every practice. Throughout the implementation phase, information about interventions offered to each patient will be collected with a standardized checklist filled out by the CDPM professionals after each appointment to ensure the fidelity of the intervention [55].

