**Figure 2 F2:**
[figure not shown]
Study timeline.

Finally, a quasi-experimental design with a non-equivalent group will be used to evaluate mid-term effects. The control group (Group C) will come from the PRECISE research program platform (main investigators: [name] and [name], http://www.programmeprecise.ca) [61]. The PRECISE study is a cohort of 2197 adults aged 25-to-75 years followed for 4 years. The target population is community-dwelling adults undifferentiated by disease, who sought primary health care locally, did not suffer from major cognitive impairment, and were able to respond to written and oral questions in English or French. Participants were randomly selected within the geographic boundaries of four local health care networks in Québec (Canada). At recruitment (T0), cohort participants reported on sociodemographic information, functional health and health care use. Two weeks (T1), 3 months (T2) and 12 months (T3) after recruitment, they completed a self-report questionnaire on their current health, health behaviours and primary health care experience in the previous year. Use of medical services is confirmed through the review of administrative databases. As in the present study, the PRECISE cohort’s main dependent variable is functional health status and quality of life which are measured with the second version of the Short-Form-12 survey (SF-12v2) [62,63]. Comorbidity is measured using the validated Disease Burden Morbidity Assessment [64]. Lifestyle and health behaviour (eating habits, physical activity, smoking and alcohol consumption) are measured using the Behavioral Risk Factor Survey System Questionnaire [65]. This unique longitudinal cohort in Canada that is providing valuable information on the effectiveness of care in the general population rather than in clients of selected care models will offer us the opportunity to measure health care experience and to quantify the impact of introducing different models of CDPM services.

Patients from this cohort will be matched with patients from Group A by age, gender, diagnosis and family income. Groups will be compared on the basis of changes over a year.

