##### Data analysis

We will first describe participants’ characteristics in each group, using means and standard deviations for continuous variables, and percentages for categorical variables. The *t*-test (for continuous variables) and the chi-square test (for categorical variables) will be used to compare baseline characteristics across study groups.

To evaluate short-term effects, Groups A and B will be compared on T2 scores (continuous variables such as self-efficacy, health education impact) with an analysis of covariance (ANCOVA) adjusted for T1 scores [72]. If the groups differ at baseline despite randomization, the ANCOVA will also be adjusted for the relevant variables [73]. The independent variable “Group” will be tested for significance at the 5% level.

To document effects over a year, a repeated measures analysis of variance will be used to study the evolution of continuous variables collected three times in Group A [74]. Mid-term effects will be evaluated by comparing T3 measurements in Group A (modifiable risk factors, functional health status and psychological well-being) with the same variables measured in Group C (from the PRECISE cohort) using an ANCOVA adjusted for T1 scores and non-equivalent baseline characteristics (variables not used for matching) [73]. Since groups A and C will be matched on four variables only, they will be considered independently in the analysis. Again, the variable “Group” will be tested for significance at the 5% level.

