##### Sample size and statistical power

The required sample size for the randomized clinical trial was calculated for the two main variables (measured with the SEM-CD and the heiQ) with a two-sided α = 0.05 and 80% power. First, for continuous scores, 64 participants in each group will allow to detect a medium effect size (ES=0.5) [75]. In addition, for the heiQ, results are also expressed as the percentage of patients improving at least half a standard deviation. In a before–after study, 35% of patients receiving the intervention presented an improvement of this magnitude [69]. Using these data in a conservative scenario providing for improvement in 20% of control participants, 138 patients are required in each group to detect a 15% difference. Accounting for an anticipated drop-out rate of 15%, 326 patients will be randomized, 163 in each group. A smaller ES of 0.34 will thus be detectable for continuous scores.

Comparison of the 138 subjects in Group A, re-measured at T3 to the same number of subjects selected in the PRECISE cohort, will also allow detection of an ES of 0.34 when measuring mid-term effects (α = 0.05, power = 80%). An additional 15% will also be enrolled in anticipation of withdrawals.

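### The one-year Group A versus PRECISE comparison has no setting term, and its detectable effect of 0.34 assumes 276 independent patients although setting is not balanced between the groups

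*Protocol article*

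**What the plan says.** The Sample size section of the protocol article states that 138 Group A patients "re-measured at T3 to the same number of subjects selected in the PRECISE cohort, will also allow detection of an ES of 0.34", with 5% significance and 80% power. No ICC or design effect is mentioned.

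The Data analysis section under Evaluation of effects names the model. T3 values in Group A are compared with Group C "using an ANCOVA adjusted for T1 scores and non-equivalent baseline characteristics", and the group variable is tested at the 5% level. No clinic or network term appears.

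Group A is recruited from eight clinics in the Saguenay region. Group C comes from PRECISE, whose participants were "randomly selected within the geographic boundaries of four local health care networks in Québec" (Evaluation of effects). Patients are matched on diagnosis, age, gender and income, not on setting.

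The text after Table 2 (Implementation evaluation) says that "heterogeneity that may be observed and documented between clinics in terms of outcomes produced" belongs to the pragmatic design, and expects common training of practitioners to reduce clustering. The Limitations section adds that the intervention may vary by setting and that each setting has its own context.

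**The concern.** Patients of one clinic share physicians, referral habits and local services, so their outcomes tend to be correlated. In the randomized A versus B comparison both arms are drawn from the same clinics, so ordinary clinic effects largely cancel, and this point does not concern it.

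In A versus C nothing balances the groups within setting. Between-setting variance enters the difference between the groups, while a patient-level ANCOVA leaves it out of the standard error. Training can reduce variation in how the intervention is delivered. It cannot remove existing differences between clinics, and it does not reach Group C.

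Group B receives the intervention after three months. A versus C is therefore the only planned between-group test of health behaviour, functional status and psychological well-being at one year. Too small a standard error there means confidence intervals that are too narrow and false positive findings above the nominal rate.

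**Working it through.** **Inputs from the protocol.** n = 138 per group after drop-out; α = 0.05; power 80%; eight clinics in Group A; four networks in Group C. The test is stated to be two-sided for the randomized comparison, and I assume the same here.

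**Assumptions, because the documents give no figure.** The ICC is 0.01 to 0.05, on the scale of the model residuals. Patients are spread evenly: 138/8 = 17.25 per clinic and, where Group C is treated as clustered, 138/4 = 34.5 per network with the same ICC. No setting is shared between the groups.

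**The plan's own figure.** (1.96 + 0.84) × √(2/138) = 0.337, or 0.338 with the t distribution. Power at 0.34 is 80.6% (80.4% with t). So 0.34 is the result for independent patients, a design effect of 1 and no gain from the T1 covariate.

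**With clustering.** The design effect (DE) in a group is 1 + (m − 1) × ICC.
- Group A: 1 + 16.25 × ICC, which is 1.163 at ICC 0.01 and 1.813 at 0.05.
- Group C by network: 1 + 33.5 × ICC, which is 1.335 and 2.675.

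The average DE over the two groups multiplies the variance of the difference. Detectable effect = 0.337 × √DE. True type I error of the independent-patient test = 2 × [1 − Φ(1.96/√DE)].

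| Case | ICC | Average DE | Detectable effect (80% power) | Power at 0.34 | Type I error |
|---|---|---|---|---|---|
| Only A clustered | 0.01 | 1.081 | 0.351 | 77.5% | 5.9% |
| Only A clustered | 0.02 | 1.163 | 0.364 | 74.5% | 6.9% |
| Only A clustered | 0.05 | 1.406 | 0.400 | 66.3% | 9.8% |
| A and C clustered | 0.01 | 1.249 | 0.377 | 71.5% | 7.9% |
| A and C clustered | 0.02 | 1.498 | 0.413 | 63.6% | 10.9% |
| A and C clustered | 0.05 | 2.244 | 0.505 | 47.0% | 19.1% |

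These are normal approximations. With 8 + 4 − 2 = 10 degrees of freedom, the detectable effects in the second case become 0.418, 0.458 and 0.561. A simulation of the patient-level ANCOVA (4,000 runs) for the second case gave type I errors of 7.4% and 18.8% at ICC 0.01 and 0.05, close to the formula.

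**T1 adjustment.** At an assumed T1–T3 correlation of 0.5 the detectable effect is multiplied by √(1 − 0.25) = 0.866. By normal approximation this gives 0.326, 0.357 and 0.438 with both groups clustered, and 0.304, 0.315 and 0.346 with only Group A clustered. The factor shrinks the true and the assumed standard error alike. Their ratio √DE, and with it the type I error, does not change.

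**The case against.** The strongest reply has four parts.

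- **Nesting is not established.** A reader might infer that every clinic or network lies wholly in one group. The protocol does not say so: the four networks are not named, and overlap with Saguenay or with the eight clinics is neither stated nor excluded. This stands. Overlap would give only partial cancellation, however, because the groups are not balanced within setting.
- **The larger figures rest on a weak picture of Group C.** Nothing shows that the matched patients fill four networks evenly, or that a geographic network has an ICC as large as a clinic's. This stands too, which is why the case with only Group A clustered is shown beside it. At ICC 0.01 that case moves the detectable effect only from 0.34 to 0.35.
- **The stated power may still be met.** The 0.34 takes no credit for the T1 covariate. At a correlation of 0.5, values near or below 0.34 are reached in several of the cases above. So the documents do not support a claim that the power is certainly lost. On about 10 degrees of freedom with both groups clustered, though, the same factor gives 0.418 × 0.866 = 0.36 to 0.561 × 0.866 = 0.49. In no case is the 5% level restored.
- **The comparison is an additional strand.** The trial is sized on the randomized comparison, and Group C is openly called non-equivalent. That limits the weight of the point but does not make the standard error correct.

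A reader might also take the sentence in Data analysis about handling groups A and C independently as a claim that patients within a clinic are independent. It concerns the decision to ignore the matching. Independence within settings follows instead from the absence of any setting term.

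**Conclusion.** The concern holds in a conditional form. The 0.34 is arithmetically right for independent patients, but the protocol's own expectation of differences between clinics undermines that assumption, and neither the model nor the matching deals with it. For any ICC above zero, the A versus C standard error is too small and the 5% test too liberal.

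The size cannot be fixed from the documents. At an assumed ICC of 0.01 to 0.05, type I error is roughly 6% to 10% on the more cautious assumption that only Group A is clustered. The figures up to 19% need the further, unsupported assumptions about Group C and should be read as an upper scenario. Loss of power is possible but not shown, since it depends on the unknown T1–T3 correlation as well as on the ICC.

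**What to change.** **Data analysis (Evaluation of effects).** Fit the A versus C ANCOVA with a random intercept for clinic in Group A, and for network or practice in Group C where PRECISE holds the identifier. If it does not, treat Group C as unclustered and allow group-specific variances. Use small-sample degrees of freedom such as Kenward–Roger.

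**Sample size and statistical power.** State that 0.34 for this comparison assumes no clustering and no gain from T1 adjustment. Add the detectable effect for declared ICCs and a declared T1–T3 correlation, computed on the same degrees of freedom as the analysis. The normal-approximation figures above should not be pasted in as they stand.

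**Cost.** The change needs analysis wording, a less favourable or more conditional effect size, and a check of which setting identifiers PRECISE holds. No new patients are needed. Intervals will be wider, with few settings to estimate the between-setting variance. The setting term corrects the standard error only. It does not remove confounding by data source, which still depends on the matching and the covariates.

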### Limitations and biases

Although conducting a randomized clinical trial may present a challenge in clinical settings where some patients receive an intervention (Group A) while others are waiting for the intervention (Group B), the short period of time between randomization and the second measurement will limit the possibility of co-interventions and maturation biases. Nonetheless, given the pragmatic nature of the trial, patients will be free to seek information beyond the proposed intervention. This may contribute to improve the observed effect. Co-interventions will be evaluated by questionnaire and will be taken into account in the analysis. In addition, analysis of the implementation will bring qualitative insight to this phenomenon. The repetition of the questionnaires may induce a learning effect; however, the time between each execution is long enough to reduce it.

The study design and its short term outcomes measure have been developed specifically to address the problem of the short period between T1 and T2. The project’s proposed two-year timeframe does not allow any exploration of the long-term efficacy of interventions on the use of the health care system.

The intervention may differ from one setting to another, but action will be taken to minimize this risk. We will outline the major considerations that may contribute to a variation in intervention or its fidelity at each stage.

The decision to measure psychosocial outcomes only is based on theoretical reasons that such outcomes are particularly pertinent to examine the adoption and maintenance of a healthy lifestyle and a better quality of life.

One potential bias is the recruitment bias, where health care providers recruit differently depending on their practice, which leads to selection bias and lack of comparability [76]. Recruitment for the present study is prior to allocation which will be provided by the research team. We will pay particular attention to find out whether patients are comparable from one participating setting to another as each primary health care professional will select and refer his or her patients and each participating setting has its own distinct contextual variables.

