To comply with the pragmatic nature of the intervention, it is up to the referring professional (primary care physician or nurse) to determine eligibility. For each patient, the referring professional will request the patient’s authorization to disclose his or her contact information to the research team and then complete a referral form. Patients refusing to take part in the study will still be eligible to receive the intervention without being involved in the evaluation process. Two patients from the same family can receive the intervention, but only one (randomly selected) will be asked to participate in the research project.

Patients agreeing to participate will complete an initial set of questionnaires at baseline (T1) collecting the main variables and sociodemographic data. Patients will be randomized to receive either the intervention within a short period of time (Group A) or later (three months later for Group B). At time 2 (T2), which will occur three months after the intervention for Group A or immediately before the intervention for Group B, patients will complete the second evaluation questionnaire. Baseline measures will be used to document equivalence between groups while T2 measures will enable the assessment of the effect after three months. A short questionnaire documenting co-interventions will also be administered at T2 (Table 3). Co-interventions represent any additional health care or CDPM services and/or therapeutic procedures other than those that are formally included in the study and may introduce confounding variables that could potentially affect the validity of the results of this study.

**Table 3 T3:** Variables and outcome measures

**Short-term:** Key measurements of effect (measured at T1 and T2 in Groups A and B)	
Self efficacy	The Self-Efficacy for Managing Chronic Disease (SEM-CD) scale (6 items) developed by the Stanford Patient Education Research Center [67].
Empowerment	Proxy of “The Health Education Impact questionnaire (heiQ)” [77]
Comorbidity	The Disease Burden Morbidity assessment (DBMA) [64]
**Mid-term:** Key measurements of effect (measured at T1 and T3 in Groups A and C)	
Health behaviour	Behaviour Risk Factor Survey System Questionnaire (eating habits, physical activity, smoking and alcohol consumption) [65]
Functional health status/quality of life	SF -12 [63,78]
Psychological well-being	K-6 [62]
Comorbidity	The Disease Burden Morbidity Assessment (DBMA) [64]

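### Co-interventions recorded at T2, after open allocation, are called a source of confounding and are to be taken into account in the analysis; if entered in the A–B ANCOVA they could bias the randomised estimate in either direction

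*Protocol article*

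**What the plan says.** Three places in the protocol article bear on this point.

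- **Evaluation of effects (objective 2).** Timing: "A short questionnaire documenting co-interventions will also be administered at T2". Co-interventions are defined there as care or services outside those formally in the study, which "may introduce confounding variables that could potentially affect the validity of the results of this study". The same section says that patients and providers know the allocation and that Group B waits three months.
- **Limitations and biases.** In a paragraph that opens with Group A being treated while Group B waits, the article notes that patients may look for information elsewhere and that this may improve the observed effect. It continues: "Co-interventions will be evaluated by questionnaire and will be taken into account in the analysis". Qualitative insight from the implementation analysis is then offered as an addition.
- **Data analysis (quantitative).** Groups A and B are compared on T2 scores by ANCOVA adjusted for T1 scores and, if the groups differ at baseline, for the relevant variables. Co-interventions are not mentioned.

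**The concern.** A confounder of the A–B contrast would have to influence which arm a patient enters. Allocation is random and co-interventions come after it, so they cannot do that. They can be a consequence of allocation. A patient told to wait three months may turn to the existing regional services, and a patient in Group A may reach other services through the clinical coordinator, whose role covers transition to specialised care.

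Conditioning on such a variable has two effects. It removes whatever part of the difference between arms runs through co-intervention use. It also makes users and non-users comparable across arms only if nothing unmeasured, such as motivation, drives both use and the T2 score. The result is no longer the pragmatic effect that the design is built to estimate.

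The method is also left open between two sections. One analyst could fit the baseline-only ANCOVA and another could add the T2 questionnaire, each citing the article, and they could report different estimates from the same data.

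**Working it through.** **1. The plan's own figures.** From Sample size and statistical power, the calculation is made "with a two-sided α = 0.05 and 80% power".

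- Responders. The article assumes "improvement in 20% of control participants, 138 patients are required in each group to detect a 15% difference", with 35% in the intervention group. For 35% v 20%, mean 27.5%: n = [1.96·√(2·0.275·0.725) + 0.8416·√(0.35·0.65 + 0.20·0.80)]² / 0.15² = (1.238 + 0.524)² / 0.0225 ≈ 138 per group. This matches.
- Drop-out, assumed to be 15%: 138/0.85 = 162.4, so 163 per group and 326 in total. This matches.
- Continuous scores, ES 0.5: 2·(1.96 + 0.8416)²/0.25 = 62.8, so 63 by the normal approximation against the stated 64. This agrees within rounding of the method.
- Detectable ES with 138 per group: (1.96 + 0.8416)·√(2/138) = 2.8016·0.1204 = 0.337, stated as 0.34. Power at 0.34 is 0.806.

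The sample size stands and this point does not change it. The value 0.34 serves below as the yardstick.

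**2. What cannot be taken from the article.** It gives neither co-intervention uptake by arm nor its effect on the scores. The following are assumptions:

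- uptake pA and pB between 10% and 30%;
- co-intervention effect g of 0.2 or 0.4 SD;
- an unmeasured common cause U with loading u of 0, 0.3 or 0.5 SD on the outcome and, where u > 0, a log-odds ratio of 1 per SD on uptake;
- direct effect of the intervention 0.34 SD.

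T1 was not modelled, so u should be read as what remains after T1 adjustment.

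**3. Formula.** With Y = 0.34·A + g·M + u·U + error, where M is co-intervention use:

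- total randomised effect = 0.34 + g·(pA − pB);
- adjusted coefficient − total effect = b·(pB − pA), where b is the within-arm slope of Y on M.

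With no shared cause, b = g, so the shift is 0.2 × 0.10 = 0.02 at the low end and 0.4 × 0.20 = 0.08 with the larger effect and gap. A shared cause makes b larger than g.

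**4. Simulation, 1,000,000 patients per scenario.**

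| Uptake A v B | Adjusted coefficient minus total effect (SD) |
|---|---|
| 20% v 20% | 0.000 to 0.003 |
| 20% v 30% | +0.020 to +0.083 |
| 10% v 30% | +0.040 to +0.166 |
| 30% v 20% | −0.022 to −0.083 |
| 30% v 10% | −0.040 to −0.167 |

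The extreme cases (g = 0.4, u = 0.5):

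- 10% v 30%: total 0.34 + 0.4·(−0.20) = 0.26; unadjusted estimate 0.258; adjusted 0.426. The implied slope is b = 0.166/0.20 = 0.83, about twice the assumed true effect of 0.4.
- 30% v 10%: total 0.34 + 0.4·0.20 = 0.42; unadjusted 0.420; adjusted 0.253.

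The analysis without the covariate recovered the total effect within simulation error (at most 0.005) in every scenario.

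**5. Consequence for the test.** With 138 per group and unit SD, the standard error is about √(2/138) = 0.12. If the total effect were zero and adjustment shifted the estimate by 0.10 SD, the shift would be 0.10/0.1204 = 0.83 standard errors. The two-sided rejection rate would be P(Z > 1.13) + P(Z < −2.79) ≈ 0.13 instead of 0.05.

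**The case against.** The strongest reply is that the article never says co-interventions enter the A–B model. The section that governs the analysis lists only T1 scores and baseline variables. Being taken into account could mean tabulation, a sensitivity analysis or interpretation; the sentence sits under limitations and names no method; and an article may leave such detail to a fuller document. The remark about confounding refers to the study as a whole, which includes a non-randomised A–C comparison where confounding is a real issue. The article also expects the short T1–T2 interval to limit co-interventions.

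Much of this stands. A reader might infer that the plan commits to adjustment and so biases the A–B effect, usually upward because waiting patients seek more help. The documents do not support that. No method is stated, bias needs both adjustment and arm-dependent uptake, and no uptake figures are given. The article's own remark that outside information-seeking may improve the observed effect would fit higher use in Group A at least as well, in which case adjustment would lower the estimate.

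It does not dispose of the point. The limitations paragraph is about Group A against waiting Group B, and it offers qualitative insight in addition to the analysis it promises, so quantitative adjustment of that contrast is the natural reading. The questionnaire is given at T2, and the article does not list it among the PRECISE measures, so an A–C reading fits less well; co-interventions during follow-up are post-exposure there too. The confounding rationale, applied to A–B, is a wrong statement and not a missing detail.

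**Conclusion.** The point holds as a conflict between sections together with a mistaken rationale. Post-randomisation co-interventions cannot confound the A–B contrast, and the promise to take them into account is not reconciled with an ANCOVA that lists only baseline covariates. If they were used as covariates and uptake depended on arm, the estimate would no longer be the total pragmatic effect and could move either way.

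The size is conditional throughout. Under the assumptions above the largest shift is about 0.17 SD, half of the detectable 0.34 (0.17/0.34 = 50%); the smallest with unequal uptake is about 0.02 SD (6%); with equal uptake there is essentially none. These figures show what is at stake and do not predict this trial. The stated sample size is unaffected.

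**What to change.** Reconcile Evaluation of effects (objective 2) and Limitations and biases with Data analysis, along these lines:

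- The main A–B ANCOVA contains pre-randomisation covariates only.
- Co-interventions up to T2 are tabulated by arm and treated as part of the strategies being compared.
- Any A–B analysis adjusted for co-interventions is labelled exploratory and is not used for the conclusion.
- The description of co-interventions as a source of confounding is dropped for the A–B comparison.

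The cost is wording only. The questionnaire, visit schedule and sample size stay as they are.
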